Perkins et al. (2008, 2010a) conducted two studies to validate this new screening methodology, one using nicotine patch and the other varenicline. In both studies, smokers with high and low intrinsic motivation to quit were recruited. Additionally, half of each group was randomly assigned to receive either $12 per day for maintaining tobacco abstinence or no reinforcement. Using a crossover (within-subjects) design, participants were randomized to receive either active medication first followed by placebo or placebo first followed by active medication. Participants attempted to quit smoking for one week while on medication and placebo. Perkins et al. (2008) reported that nicotine patch doubled days of tobacco abstinence in smokers with high motivation to quit compared to placebo (2.0 ± 0.3 days for nicotine vs. 1.1 ± 0.2 days for placebo). Similarly, Perkins et al. (2010a) showed that varenicline increased days of abstinence in smokers interested in quitting compared to placebo (2.6 ± 0.3 days for varenicline vs. 1.5 ± 0.2 days for placebo). These data indicate that even on medication, participants were not tobacco abstinent on the majority of days, mirroring high relapse rates during the first week of a quit attempt (Fiore et al. 2008). In the varenicline study, Perkins et al. (2010a) found that among those who initiated abstinence during the quit week, 70% on varenicline and 88% on placebo relapsed. Thus, this 1-week quit attempt appears to be a valid model of real-world abstinence success.

Mediators of Treatment Efficacy

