The primary advantage of using a crossover or within-subjects design is efficiency. Greater statistical power can be achieved with a smaller sample size compared with between-subjects or parallel-groups designs, which require more subjects to overcome large inter-subject variability. Additionally, because each participant serves as his or her own control in a crossover study, matching on sociodemographic and smoking history variables that might confound outcome measures is not necessary.

Crossover designs are best suited to short-term outcome studies of chronic diseases that persist throughout active drug and placebo phases (Sibbald& Roberts 1998; Woods et al. 1989). Tobacco smoking is a chronic, relapsing disease (Fiore et al. 2008). Smoking cessation medications can temporarily help smokers become abstinent, but when the medication is stopped, smokers are able to return to baseline smoking during a washout period (Perkins et al. 2008, 2010a). During quit attempts, relapse is common even while still on medication (Fiore et al. 2008).

However, there are some issues that could preclude using a crossover design. One obvious concern is the possibility of carryover effects of the drug itself or any drug-induced changes in the outcome measures (Sibbald& Roberts 1998; Woods et al. 1989). The plasma half-life of gemfibrozil is 1.5 hours, so systemic concentration declines rapidly. There is no evidence, to our knowledge, that gemfibrozil causes permanent or long-lasting changes in neuronal or physiological systems. As stated above, any changes in smoking behavior due to the medication can be reversed when participants resume to ad libitum smoking in the crossover phase. In this study, participants will be told that they do not have to resume smoking if they achieve abstinence in the first phase, but they will not be able to continue in the study. To test for carryover effects, data will be analyzed for order of treatment condition.

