The crossover design creates a special case in which a participant may successfully maintain abstinence during the first quit attempt. Although participants always have the autonomy to discontinue study participation, this is one situation where it could benefit them to do so. Thus, participants who successfully maintain abstinence during the first phase will meet with the PI or their designee to discuss discontinuing their participation. Participants will be informed of the dangers of returning to smoking and the benefits of continued abstinence. Participants will be informed of the treatment opportunities that are available to them, but that they cannot continue on study medication. Referrals for further treatment, both pharmacological and behavioral, will be provided. Participants will be encouraged to drop out of the study and continue smoking abstinence, but will not be arbitrarily discharged from the study. This procedure strikes a balance between two fundamental ethical principles of clinical research, beneficence and respect for the autonomy of the participant.

Withdrawal of subjects:

Stop points for withdrawing participants from the study include: 1) at the request of the participant, 2) if the participant is unable or unwilling to comply with study requirements and procedures, 3) any occurrence that in the opinion of the investigators would compromise the health of the participant, 4) any serious adverse effect; and 5) a successful quit attempt after the first phase of the study, meaning that the participant does not complete the second phase of the study.

When a subject is withdrawn from a study, data collection will cease with the exception of monitoring for adverse events and follow-up to check up on health, especially in the event where the participants withdrew for health reasons. Subjects will be replaced in the sense that attempts will be made to meet the target enrollment and continue to recruit until this has been met.

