**Statistical Analysis**

Standard techniques will be used to examine the distributional properties of the data (means, standard deviations, medians, skewness, kertosis) in order to verify that all assumptions are met for subsequent analyses. The data will be examined for univariate and multivariate outliers. For all analyses, results are considered significant at *p*<.05.

Aim 1:Investigate the effect of gemfibrozil on laboratory measures of nicotine reinforcement and cue-elicited craving

The percentage of puffs chosen from Nic cigarettes in the forced-choice sessions will be analyzed using mixed-model analysis of variance (ANOVA) with drug condition (placebo, gemfibrozil) as within-subject factors and order of exposure of drug condition and order of exposure of cigarette type (Nic, Denic) as between-subject factors. For cue-reactivity sessions, self-report and physiological measures will be analyzed by mixed-model ANOVA, with drug condition (placebo, gemfibrozil), cue type (smoking, nonsmoking) and time post-cue (0, 15 minutes) as within-subject factors and order of exposure of drug condition and cue type as between-subject factors. For measures showing significant main effects or interactions, post hoc comparisons between means will be conducted. Supplemental analyses may be conducted using bivariate analyses to identify relationships to participant-level variables (e.g., socioeconomic factors, mood). Variables identified will be used as covariates if they are believed to be suppressor variables or entered into stepwise regressions to better characterize the participants for whom gemfibrozil has the greatest effect on laboratory measures.

Aim 2: Screen for the ability of gemfibrozil to aid smoking abstinence during a brief quit attempt

Data from the quit-attempt will be analyzed using mixed-model ANOVA with drug condition (placebo, gemfibrozil) as a within-subject factor and order of exposure of drug condition as a between-subject factor. Post hoc comparisons between means will be conducted on significant overall effects. Supplemental analyses may be conducted using bivariate analyses to identify relationships to participant-level variables (e.g., socioeconomic factors, mood). Variables identified will be used as covariates if they are believed to be suppressor variables or entered into stepwise regressions to better characterize the participants for whom gemfibrozil facilitates smoking abstinence.

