Aim 3: Examine the validity of using laboratory measures of tobacco dependence to predict smoking abstinence and possible gemfibrozil-related increases in smoking abstinence

Bivariate correlational analyses will be used to determine the predictive association between laboratory measures of nicotine reinforcement and cue reactivity and tobacco abstinence during the quit-attempt. Two multivariate stepwise regressions will then be constructed to determine multivariate predictors of abstinence days and gemfibrozil-related change in abstinence days. At step one, demographic variables will be entered. At step two, smoking-related characteristics that are significantly associated with abstinence will be entered. Finally, at step three, measures of laboratory performance in both forced-choice and cue-reactivity that were significant in bivariate analyses will be entered to determine their multivariate predictive validity for smoking abstinence.

Power Analysis

Based on the preclinical data, we expect that gemfibrozil will decrease cue-reactivity, the number of puffs taken on the nic cigarette and increase abstinence. The preclinical data suggest that observed effect size of those effects will be around 0.5. However, those effect sizes may be lower in human subjects. As we have currently no data on human subjects, we decided to power the study to be able to detect a smaller effect size. Taken into account the variance of the behavioral responses based on the previous human laboratory studies (McKee et al., 2011), with 40 subjects, we will have sufficient power (>80%) at an alpha level of 0.05 to detect differences between conditions (gemfibrozil vs placebo) as small. This study will provide the necessary data to determine the effect size of gemfibrozil on these measures and preliminary evidence on the potential utility of gemfibrozil as a smoking cessation pharmacotherapy. Based on the results obtained, we can submit further grants to conduct a clinical trial to investigate the efficacy of gemfibrozil as a smoking cessation medication.

Missing, unused and spurious data:

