Missing data will be dealt with according to statistical principles for filling in missing cells. In the event that large amounts of data are missing due to, for example, participant noncompliance with study procedures, the data will be analysed according to the primary goals of the study and the objectives of this study. Statistical procedures that deviate from the protocol will be reported and justified in a protocol deviation log.

The data from all eligible subjects will be included in the data analysis

Accrual Number

There are several factors that could adversely affect accrual and completion of this study: a) participants may quit during the first medication phase; b) some participants might experience intolerable side effects of gemfibrozil; and c) some participants might not be compliant with taking medication. Given these factors, we anticipate up to 50% attrition. Drop-outs will be replaced.

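### Whether a phase-1 quitter stays in the trial is contradictory, and the within-subject ANOVA with filled-in cells is a poor rule for dropout that depends on abstinence

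*Protocol*

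**What the plan says.** Three places in the protocol deal with a participant who quits in phase 1.

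- Introduction, Considerations of a Crossover Design: those who become abstinent need not resume smoking, "but they will not be able to continue in the study".
- Participant Safety Monitoring, Successful Quit Attempts: "Participants will be encouraged to drop out of the study and continue smoking abstinence, but will not be arbitrarily discharged from the study".
- Participant Safety Monitoring, Withdrawal of subjects: the fifth stop point is "a successful quit attempt after the first phase of the study, meaning that the participant does not complete the second phase of the study".

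After withdrawal, only adverse-event and health follow-up continues, and recruitment goes on until the enrolment target is met. No section defines a successful quit attempt.

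For Aim 2, the Statistical Analysis section states: "Data from the quit-attempt will be analyzed using mixed-model ANOVA with drug condition (placebo, gemfibrozil) as a within-subject factor", with order of drug condition as the between-subject factor. On missing data it says: "Missing data will be dealt with according to statistical principles for filling in missing cells". It adds that all eligible subjects enter the analysis. The Accrual Number paragraph allows up to 50% attrition, names quitting in phase 1 as one cause, and says drop-outs are replaced.

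**The concern.** The fifth stop point is unconditional, while the paragraph on successful quitters leaves the decision to the participant. Two identical participants could be handled differently, and the handling decides who has phase-2 data. The rule acts on the outcome itself: those with the best phase-1 result are the ones who lose phase 2.

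The analysis text does not meet this situation. A factorial ANOVA on completed cells needs both phases from each person. If incomplete people are left out, the phase-1 successes go with them. If their cells are filled with single values and treated as observed, the standard error is too small. The protocol intends the results to supply an effect size for planning a further trial, so an attenuated estimate or a false positive would carry into that decision.

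**Working it through.** **Plan's own figure.** The power paragraph claims "sufficient power (>80%) at an alpha level of 0.05" with 40 subjects. The document at hand gives no number for the detectable effect. Reading the preclinical 0.5 as a standardised within-person difference, a two-sided paired t-test (noncentrality 0.5 × √40 = 3.16) has 86.9% power, consistent with the claim. With the 30 completers of the enrolment table it is 75%. This does not address who is missing.

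**A. Loss of quitters and the estimate for days abstinent**

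Inputs from the Introduction: 2.6 vs 1.5 days (varenicline screening study) and 2.0 vs 1.1 days (patch study). Assumed, not in the documents: latent SD 4–6 days, within-person correlation 0.3–0.6, success taken as 7 of 7 days, 20 participants per sequence.

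Model: days = floor(a + u + e), limited to 0–7, where u is the person effect, e the phase error, and a is set to reproduce each mean. With d = phase 1 − phase 2, the effect is estimated as [mean d (drug first) − mean d (placebo first)] / 2.

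Removing people with seven days in phase 1 lowers mean d in both sequences, but more in the drug-first sequence, so the difference shrinks. With 2.6 vs 1.5 days, 13–20% have seven days on drug and 5–9% on placebo. If all of them leave:

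| Analysis | Estimate (true 1.10) | Change |
|---|---|---|
| Completers only | 0.85–1.00 | 9–23% too small |
| Phase 1 carried forward | 0.76–0.92 | 16–31% too small |
| Sequence-mean fill | 1.13–1.21 | 3–10% too large |
| Likelihood, all observed phases | 1.07–1.09 | 1–3% too small |

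Change is 1 − estimate/1.10; for example 1 − 1.00/1.10 = 9%. The far end for completers lay between 21% and 23% in repeated runs, so I quote about 9–22%. With 2.0 vs 1.1 days, completers give 0.72–0.82 against 0.90 (9–20% too small). If half the quitters leave, completer bias is about 4–9%. With no true effect, quitter loss alone leaves type I error at 0.05–0.06 for every method.

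Sensitivity to the outcome model: the Introduction reports that among initiators of abstinence "70% on varenicline and 88% on placebo relapsed", so 30% and 12% did not. Assuming 60–70% initiate, 18–21% and 7–8% would leave. A model matched to those shares gave completers 0.80–0.93 (15–27% too small) and a mixed model 0.98–1.04 (5–11% too small). I do not rest the size on it: the initiation share is not in the document, and an initiator who did not relapse need not have been abstinent on all seven days.

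**B. Filling cells and type I error**

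The approved ceiling is 40 enrolled and 30 completers: (40 − 30)/40 = 25% lost. The Accrual Number ceiling is 50%.

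Take unit variance, correlation ρ, n per sequence, a fraction m of phase-2 cells missing at random and filled with the sequence mean. Per sequence:

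- true variance of mean d = [1 + 1/(1 − m) − 2ρ]/n
- variance the ANOVA uses ≈ [(1 − m) × 2(1 − ρ) + m]/n

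With ρ = 0.5:

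- m = 0.25: true 1.333/n, used 1.000/n. The SE is too small by √(1/1.333) = 0.866. The critical value 2.024 (38 df) acts as 1.753, so type I error is about 8%.
- m = 0.50: true 2/n, used 1/n. The factor is 0.707 and the critical value acts as 1.431, so type I error is about 15%.

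Simulation with n = 40 agrees: about 8–10% (mean fill) and 11–13% (regression fill) at 25%; 16–17% and 23–29% at 50%.

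**C. Primary laboratory measures.** They are taken at the end of medication week 1, before the quit week, so a quitter keeps the phase-1 value. With an assumed correlation of up to 0.5 with quitting, completer bias was 4% or less. Mean filling gave type I error of 0.06–0.08 at 10–15% loss and 0.14–0.16 at 46% loss.

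**The case against.** The strongest reply is that the protocol fixes neither a complete-case analysis nor a filling method. It includes all eligible subjects, a mixed-model ANOVA can be fitted by likelihood, multiple imputation could count as filling cells, and a SAP may settle this. That stands, and it makes the bias conditional. It does not clear the text: a likelihood model has no cells to fill, so the two sentences read together point to an ANOVA on completed cells, or at least allow one.

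The Introduction sentence can be read as covering only people who choose to stay abstinent, which fits voluntary exit. That also stands; the firm conflict is between the fifth stop point and the paragraph on successful quitters.

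A reader might infer more than the documents support:

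- that removing quitters causes false positives. It does not; the inflation comes from single-value filling under overall attrition.
- that filling cells shrinks the effect. Mean fill moves it slightly away from zero; completers-only and carry-forward shrink it.
- that the primary comparison loses the drug's clearest successes. Their phase-1 laboratory values are already recorded, and the bias is small.
- that half the phase-2 cells will be missing. The 50% is a ceiling on attrition from all causes; the enrolment table implies 25%.
- that replacement selects non-quitters. Replacements are newly recruited participants.

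**Conclusion.** The point holds in conditional form. The withdrawal rules conflict and success is undefined, so which phase-2 data exist depends on the secondary outcome and on how staff read the text. If only completers are analysed, the effect on days abstinent is understated by about 9–22%, given the cited means, departure of all seven-day quitters, SD 4–6 days and correlation 0.3–0.6; it is about 4–9% if half leave. If cells are filled with single values and treated as observed, type I error is about 8–13% at 25% missing and 16–29% at 50%, for primary and secondary outcomes alike. Neither result follows with certainty from the protocol, but nothing in it rules either out. The sizes rest on assumptions the documents do not supply.

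**What to change.** 1. Reconcile the Introduction with the two paragraphs in Participant Safety Monitoring into one rule for phase-1 quitters, and define a successful quit attempt. Which rule applies is for the sponsor.
2. Replace the sentence on filling missing cells, and the ANOVA where phases can be missing, with a likelihood-based linear mixed model: drug, period and sequence as fixed effects, participant as random effect. Use every observed phase of every randomised participant, including those who stop after phase 1 or are replaced. Allow no single-value filling; proper multiple imputation is an acceptable alternative.
3. Report the phase-1-only comparison between randomised groups as a sensitivity analysis, because removal after phase 1 cannot affect it.

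The cost is protocol wording and a standard model, with no new data and no change in sample size. The phase-1 comparison will be imprecise. The mixed model keeps some bias because days abstinent is bounded at 0 and 7: 1–3% in the main simulation, 5–11% in the model matched to the non-relapse shares. This should be acknowledged when the estimate is reported.

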Appendix 3 provides a schematic of the trial design

**Risks and Discomforts**

Minimal risks/discomforts

There is a minor risk of contact dermatitis as a result of the skin electrodes. Participants will likely experience increased tobacco craving after presentation of smoking cues. Because both Nic and Denic cigarettes are smoked during the forced-choice session, participants will not experience withdrawal. Smoking the equivalent of 4 cigarettes over 4 hours during the forced-choice session should pose little additional risk to current smokers. Because smoking is toxic to fetal development and because the effects of gemfibrozil on fetal development are not known, women must provide a negative urine pregnancy test before sessions and must not be nursing.

There is a possibility of discomfort at the site of needle entry for blood draws, and there is a risk of bruising. There is a remote risk of fainting or local infection. Trained phlebotomists and nurses using aseptic techniques will draw blood.

Participants might experience nicotine withdrawal during the quit-attempt weeks. This might include cigarette cravings, depressed mood, irritability, insomnia, anxiety, restlessness, difficulty concentrating, and increased appetite (DSM-IV symptoms of nicotine withdrawal, American Psychiatric Association 2000). These symptoms might increase the possibility of relapse to smoking.

Potential loss of confidentiality is a particular risk of studies involving genotyping. Under such circumstances, it could be a risk for genetic information about an individual to be made known. For example, genetic information could be informative to determine parentage or could be interpreted by an insurance company or employer to mean that the person was at increased risk for a problem. No genotype data will be released to subjects under any circumstance. In the study, there will be no identification of genetic diseases, and thus, no relevant information to report to subjects.

More than minimal risks/discomforts

The primary risks of this study involve gemfibrozil administration. In the Helsinki Heart Study, 2046 patients received gemfibrozil for up to 5 years. The adverse reactions that were statistically more frequent in the drug group compared with the placebo group were gastrointestinal reactions (34% vs. 24%), including dyspepsia and abdominal pain. Acute appendicitis (1.2% vs. 0.6%) and

Figure 1

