**Participant Safety Monitoring**

During screening, study applicants will undergo a complete battery of medical laboratory tests and physical exam to determine their eligibility and safety of their participation in this study (see Appendix 2). Study applicants will be excluded if they have any history of liver disease, abnormal renal function, diabetes, recent gallbladder disease or operation, or any other medical condition, or are on any medication that may contraindicate their participation in this study. During the treatment phase of the study, participants will be asked about side effects and adverse events at each clinic visit (Appendix 13). Additionally, CBC, complete metabolic panel, creatine kinase levels, PT/INR, and HbA1c will be assessed at screening and after at least 10 days on medication. The QI/PI ([name] [name]) will review side effect reports and medical tests. Participants will be discharged from the study if they have any signs or symptoms that may contraindicate continued drug administration.

If participants seek medical care during the study, they will be instructed to notify their physician or medical care provider of involvement in the study and the possibility that they may be taking gemfibrozil. We will follow up with participants 1 week after the last medication phase to assess potential side effects (see Appendix 13). The QI will review the follow-up assessment, and if there are no problems, the participant will be discharged from the study. Any medical concerns will be followed until a satisfactory resolution is reached.

Successful Quit Attempts: Ethical considerations

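### Withdrawal ends outcome collection, so quit-week abstinence after stopping is never observed and the abstinence comparison rests mainly on people who tolerate and take the capsules

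*Protocol*

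**What the plan says.** The paragraph on withdrawal of subjects (Protocol, Participant Safety Monitoring) lists five stop points. They include "if the participant is unable or unwilling to comply with study requirements and procedures" and "any occurrence that in the opinion of the investigators would compromise the health of the participant, 4) any serious adverse effect". The rule that follows is: "When a subject is withdrawn from a study, data collection will cease with the exception of monitoring for adverse events", together with follow-up of health. Earlier in the same section: "Participants will be discharged from the study if they have any signs or symptoms that may contraindicate continued drug administration". In each case the participant leaves the study, not just the medication.

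Statistical Analysis, under Accrual Number, expects such losses. Alongside quitting in the first phase it names "some participants might experience intolerable side effects of gemfibrozil" and "some participants might not be compliant with taking medication" among the reasons to anticipate attrition of up to 50%, with drop-outs replaced. Just above, under missing, unused and spurious data, missing cells are to be filled in by a method not named there, and "The data from all eligible subjects will be included in the data analysis".

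The primary laboratory measures are taken about one week into each phase. The secondary outcome, days abstinent, comes from the second week. It relies on self-report, including the daily call, and on breath CO at clinic visits.

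**The concern.** The two sections pull in different directions: one promises to analyse every eligible subject, and the other ends collection of the outcome data that the promise needs. A participant who is withdrawn on day 9 is no longer asked about smoking for the rest of the quit week and gives no CO reading at the abstinence visit.

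This is a data-collection rule. An analysis plan may name a filling method, but it cannot recover days that nobody recorded. Replacing drop-outs restores the number of participants, not the kind of participant who was lost.

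The loss may also be related to treatment. Risks and Discomforts reports gastrointestinal reactions in 34% on gemfibrozil against 24% on placebo in a long-term study, and Accrual Number attributes intolerable side effects to gemfibrozil. The Power Analysis section says that this study will supply the effect size and preliminary evidence for a later efficacy trial, so any distortion would carry into that trial's planning.

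**Working it through.** The Protocol gives no figure for the effect of this rule, so there is none to reproduce. The check has four steps.

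**1. What is lost, by time of withdrawal**

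| Withdrawal | Laboratory data of that phase | Quit-week data of that phase |
|---|---|---|
| First week of a phase | lost | all lost |
| Second week of a phase | normally already taken | remaining days and the abstinence visit lost |

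A withdrawal in the first phase also loses the whole second phase. Data collected before withdrawal are kept. The planned mixed-model ANOVA treats drug as a within-subject factor, so a person with one phase missing needs a filled cell or drops out of the contrast. A filled value has to be assumed or modelled, usually from those who stayed.

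**2. Size if the contrast rests on those who stay**

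Let D_T be the effect in those who keep taking the capsules, D_L the effect in those who stop, and p the share who stop in the gemfibrozil phase and are lost.

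- As-assigned effect = (1 - p) x D_T + p x D_L
- Overstatement factor = D_T / as-assigned effect = 1 / [(1 - p) + p x D_L/D_T]

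| p (assumed) | D_L = 0 | D_L = half of D_T | D_L = D_T |
|---|---|---|---|
| 5% | 1/0.95 = 1.05 | 1/0.975 = 1.03 | 1.00 |
| 10% | 1/0.90 = 1.11 | 1/0.95 = 1.05 | 1.00 |

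If D_T and D_L are both zero, the retained and as-assigned effects are both zero and there is no bias.

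The Protocol gives no two-week stopping rate. Its nearest figures measure something else:

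- 34% - 24% = 10 points is an excess of reactions, not of stopping, over up to 5 years.
- The anticipated attrition of up to 50% covers all causes, including first-phase quitting.
- The enrolment table plans 30 completers of 40, so (40 - 30)/40 = 25%, again from all causes.

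**3. Simulation check**

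Seven-day abstinence counts were simulated for 300,000 participants per scenario under assumed parameters: about 1.9 abstinent days on placebo, a benefit only in those who tolerate the drug, and all intolerant participants dropped.

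- 10% intolerant: a true all-randomised difference of 0.83 days became 0.92 among those retained (0.92/0.83 = 1.11).
- 25% intolerant, as a stress case: 0.69 became 0.92 (0.92/0.69 = 1.33).
- No true effect: the retained difference lay between -0.005 and +0.004 days, which is zero within simulation error.

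**4. The opposing route**

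The fifth stop point removes participants who quit successfully in the first phase. When all first-phase full quitters also left in the simulation, the retained difference fell by only about 0.01 days (for example 0.92 to 0.91). That size depends on how many quit.

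**The case against.** The strongest reply is that the hypotheses under Study Aims are framed as the effect when taking gemfibrozil, and that adherence is checked by call, pill count and plasma level. For a first screen, an on-drug effect is a defensible target. This stands, so the as-assigned result should be reported beside the on-capsule result and need not replace it. It does not remove the conflict with the all-eligible-subjects sentence.

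A reader might infer that the rule does overstate the drug's effect. The documents do not show that. It takes a real benefit in takers, a smaller one in leavers, and an analysis resting on those who stay. An inert drug would not gain a false benefit by this route. If lost days were filled as smoking, the error would run against gemfibrozil.

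A reader might also infer that missing capsules automatically means withdrawal. The stop point speaks of study requirements and procedures and does not name capsules. The daily call sheet in Appendix 15 accepts No to both medication questions and still asks for the cigarette count. Someone who misses capsules can therefore stay in; the loss begins at withdrawal. Even so, the call is tied to the capsule: the Medication compliance paragraph and Appendix 15 time it to the evening dose, and Appendix 4 makes its payment depend partly on taking the pills.

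Finally, the primary laboratory outcomes are less exposed. That stands for second-week withdrawals. It does not hold for a first-week withdrawal, or for the second-phase session of someone withdrawn in the first phase.

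**Conclusion.** The point holds for the secondary abstinence outcome and is worth a cheap correction. Once a participant is withdrawn, quit-week outcomes are not observed, and the abstinence comparison then applies mainly to people who tolerate and take the capsules.

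A bias in favour of the drug is possible but not established. If the drug helps only while taken, the factor is 1.05 at p = 5% and 1.11 at p = 10%, and it shrinks towards 1 as leavers share the benefit. It is larger if stopping is commoner on gemfibrozil, because p is then larger. The documents support such a difference only indirectly, through long-term reaction rates, and nothing in them shows that non-compliance differs by treatment.

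Putting the 50% attrition figure into the formula would give 1/0.50 = 2.0. The documents do not support that reading, because it would require every loss to be capsule stopping in the gemfibrozil phase, while Accrual Number lists first-phase quitting as well.

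**What to change.** Leave the clinical stopping rules as they are and change only what is collected afterwards.

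- In the withdrawal paragraph, separate stopping capsules from ending outcome collection. Unless the participant withdraws consent for data collection, continue the daily cigarette call to the end of that phase and hold the scheduled abstinence visit (CO, cigarette report, craving and withdrawal forms).
- Align the Medication compliance paragraph, Appendix 4 and Appendix 15 so that neither the call nor its payment depends on taking a capsule.
- Reconcile the withdrawal paragraph with the all-eligible-subjects sentence in Statistical Analysis.
- Report abstinence including these days alongside the on-capsule analysis.

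The cost is a protocol and consent amendment and some payments, since Compensation currently pays those who withdraw voluntarily only up to that point. At the listed rates the most per affected phase is $150 for the abstinence week plus 14 x $2 for calls, or $178, and replacing these participants as well adds to the total. The as-assigned effect may be smaller than the on-capsule one. The change does not supply a second phase for someone who stops in the first and does not continue, and it adds no laboratory sessions.
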